### Quality Assurance/Quality Control Measures

Study coordinators regularly inspect study facilities and documentation (eg, informed consent forms, clinic and laboratory records, other source documents, and case report forms), as well as observe the performance of study procedures. Investigators also allow inspection of all study-related documentation by authorized representatives. A site visit log is maintained at the study site to document all authorized inspection visits and audits.

On-site study monitoring is performed by site coordinators and the multisite coordinator. Monitoring includes verification of compliance with the consenting process and other human subjects guidelines; assessment of adherence to the study protocol, study-specific procedures manual, and local counseling practices; and confirmation of the quality and accuracy of information collected at the study site and entered into the study database.

All data forms are reviewed for accuracy and completeness by study staff before sending data to TUC, where data cleaning is performed. At TUC, errors identified during the data cleaning process are compiled into a quality control (QC) report and sent back to site study staff for corrections. QC reports are compiled and tracked quarterly.

### Study Retention

As this study measures person-time on and off PrEP, retention for the full study period is not a primary goal. However, to encourage participants to access prevention services and facilitate PrEP adherence, study staff make every reasonable effort to follow participants for the entire study period. A study-specific appointment and tracking system is used to ensure completion of assessments and to facilitate management of participant tracking. Tracking methods include SMS text messages, voice calls, emails, and visits to participants’ place of employment. Confidentiality for participants is maintained through outreach efforts including text messaging, phone calls, and emails that do not disclose any details of study participation and that are sent by outreach staff trained on maintaining confidentiality of participants and potential participants, using outreach method participants have selected as their preferred method (ie, SMS, voice, emails, or workplace visits).

Study staff have developed and implemented standard operating procedures for retention to minimize attrition. These procedures include thorough explanation of the study visit schedule and procedural requirements during the informed consent process and re-emphasis at each study visit; collection of detailed contact information at the study enrollment visit, and active review and updating of this information at each subsequent visit; collection of locator information from each participant, so that the participant can be found if the phone number or address changes; creation of a retention plan to maximize the level of participation in study-required visits; use of appropriate and timely visit reminder mechanisms; and immediate and multifaceted follow-up on missed visits.

### Compensation

Participants are reimbursed for their time and effort in this study and for their travel to study sites. Participants receive 1000 THB (US $35) per visit attended at 0 (baseline), 3, 6, 9, 12 months, and a courtesy award of 500 THB (US $17.50) for completing the final (12-month) visit. If the participant travels to the study site and is deemed ineligible during the screening process, he or she receives 1000 THB (US $35).

Participants receive cash compensation for responding to weekly SMS surveys. Each person receives 30 THB (US $0.83) for each SMS survey the participant completes. If a participant achieves a perfect response rate of 4 surveys per month, he or she receives a courtesy award of 100 THB (US $3.50) at the end of the fourth survey of the month.

In addition to the above compensation, participants who initiate PrEP receive 500 THB (US $17.50) at each monthly medication pickup.

To identify participants with potential acute HIV infection while being prescribed PrEP, participants with symptoms consistent with acute HIV infection are compensated 500 THB (US $17.50) if presenting to a study site before their next scheduled visit.

For participants who initiate PrEP, the total possible compensation for 1 year of follow-up is 14,360 THB (US $479), given an increased number of study visits for pill pickups. For those who choose not to initiate PrEP, the total possible compensation for one year is 8360 THB (US $279).

### Statistical Considerations

Statistical analysis uses a person-time approach to compare HIV incidence during person-time on PrEP to HIV incidence during person-time not on PrEP.

### Sample Size Calculation

This study focuses on the primary endpoint of incident HIV infection during follow-up, comparing person-time on PrEP and off PrEP. Participant uptake of PrEP, level of PrEP adherence, and cessation of PrEP use serve as secondary endpoints in this study.

As prospectively measured in the Bangkok MSM Cohort Study cohort [37], we expect that the participants will be a mixture of very high-risk MSM and TGW 18 to 24 years of age with an HIV incidence rate of 11 per 100 PY and high-risk MSM 22 to 26 years of age with an incidence rate of 5 per 100 PY. Assuming a 50/50 mixture, we expect an incident rate of 8.5 per 100 PY (range=7-10). On the basis of recent iPrEx open-label extension (iPrEx OLE) study, we assume a 50% reduction in incidence for the PrEP group versus off-PrEP group [38]. On the basis of empirical evidence, we expect that some 50% of the participants will choose to take PrEP.

The sample size of this study is 1240 participants based on the following assumptions: incidence without PrEP is 8.5 per 100 PY, a PrEP efficacy of 50%, time-on-PrEP of 50%, attrition of approximately 2% per month, power=0.8, α (one-sided)=.025, and inflation of the standard error of the hazard ratio by 0% to 20% after adjusting for confounding. From this assumption, we expect that a combined sample of 1240 (620 on PrEP and 620 not on PrEP) will be sufficient.

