Thailand has a history of long-standing community partnerships with organizations that advocate on behalf of populations that sell or exchange sex. This, coupled with the regional HIV epidemiology and cultural openness to the discussion of sex work and other forms of exchanged sex, makes Thailand an important setting for implementation science research of combination HIV prevention approaches with antiretroviral (ARV) drug–based components among young MSM and TGW who exchange sex. A large observational cohort of MSM and TGW in Bangkok has demonstrated high and sustained HIV incidence (11.1/100 person-years [PY]) among 511 young (aged 18-21 years) MSM and TGW who sold or exchanged sex. Incidence was elevated despite regular HIV testing and counseling, condom and lubricant provision, care for sexually transmitted infections (STIs), and a national program of universal and free ARV access [15]. This has direct relevance to HIV epidemics underway among young and minority MSM and TGW in multiple settings. Understanding how to reduce HIV transmission rates in these contexts is a shared scientific challenge with common features at biological, behavioral, and network levels [16,17].

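### The planning incidence of 8.5 per 100 PY does not follow from the stated 50/50 mixture of 11 and 5, which gives 8.0, yet the sample size uses 8.5

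*Protocol article*

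**What the plan says.** The Sample Size Calculation section of the protocol article builds the planning incidence from two strata. The first stratum is described as "very high-risk MSM and TGW 18 to 24 years of age with an HIV incidence rate of 11 per 100 PY". The second, older and at lower risk, is described as "high-risk MSM 22 to 26 years of age with an incidence rate of 5 per 100 PY". The section then combines them in one sentence: "Assuming a 50/50 mixture, we expect an incident rate of 8.5 per 100 PY (range=7-10"). The next paragraph carries the result into the sample size assumptions: "incidence without PrEP is 8.5 per 100 PY, a PrEP efficacy of 50%, time-on-PrEP of 50"%. Attrition and error rates are set as "attrition of approximately 2% per month, power=0.8, α (one-sided)=.025". The allowance for the adjusted analysis is given separately as "inflation of the standard error of the hazard ratio by 0% to 20% after adjusting for confounding". The outcome is a total of 1240, split 620 on PrEP and 620 off. The Abstract expresses the same target as 620 person-years in each state.

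Background reports an incidence of 11.1 per 100 PY in a Bangkok cohort, "among 511 young (aged 18-21 years) MSM and TGW who sold or exchanged sex".

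**The concern.** The section states the two rates, the weights and the result, and these do not agree. The result is not incidental: it is the off-PrEP incidence from which the expected number of infections, and so the power for the primary endpoint, follows. If the rate is too high, the trial expects more infections than its own inputs support.

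The strata are also unclear. Ages 22, 23 and 24 fall in both bands, and nothing says which rate a person of that age carries. The rate of about 11 is given for ages 18 to 24 here and for ages 18 to 21 in Background.

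**Working it through.** **1. The mixture**

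- Equal weights: 0.5 × 11 + 0.5 × 5 = 8.0 per 100 PY.
- Weight on the higher rate that gives 8.5: (8.5 − 5) / (11 − 5) = 0.583, a share of about 58/42.
- Rounding does not explain the gap. With 11.1 from Background, 0.5 × 11.1 + 0.5 × 5 = 8.05.
- 8.5 is the midpoint of the stated range: (7 + 10) / 2. The ends of that range imply shares in the higher-rate stratum of (7 − 5)/6 = 33% and (10 − 5)/6 = 83%.

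**2. Reproducing the plan's figure at 8.5**

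Inputs from Sample Size Calculation: hazard ratio 0.5, half the time on PrEP, one-sided α 0.025, power 0.80. The 620 is read as person-years per state, as in the Abstract.

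- Schoenfeld events with no inflation: 4 × (1.960 + 0.842)² / (ln 0.5)² = 4 × 7.849 / 0.4805 = 65.3.
- With 10% inflation of the standard error: 65.3 × 1.1² = 79.1 events.
- Mean rate over both states: 0.75 × 0.085 = 0.06375 per PY.
- Person-years: 79.1 / 0.06375 ≈ 1240, or 620 per state.

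The 10% is the midpoint of the stated 0% to 20%. The article does not say that it was used; it is inferred because it reproduces the target. An unpooled Wald calculation on the log rate ratio gives 577, 698 and 830 PY per state at 0%, 10% and 20% inflation, so it does not reproduce 620 at any of them.

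**3. The same design at 8.0**

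Expected infections at 620 PY per state:

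- At 8.5: 620 × 0.085 + 620 × 0.0425 = 52.7 + 26.4 = 79.1.
- At 8.0: 620 × 0.080 + 620 × 0.040 = 49.6 + 24.8 = 74.4, which is 5.9% fewer.

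Power is Φ(ln 2 / (k × SE) − 1.960), where k is the inflation factor. SE is √(4/D) for Schoenfeld, with D total events, and √(1/e₀ + 1/e₁) for Wald, with e₀ and e₁ the events off and on PrEP.

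| SE inflation | Schoenfeld, 8.5 → 8.0 | Wald, 8.5 → 8.0 |
|---|---|---|
| 0% | 86.9% → 84.8% | 82.8% → 80.5% |
| 10% | 80.0% → 77.6% | 75.2% → 72.6% |
| 20% | 72.8% → 70.2% | 67.8% → 65.1% |

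On the variant that reproduces 620, holding 80% power at 8.0 needs 79.1 / 0.060 ≈ 1318 PY, about 659 per state (8.5/8.0 = 1.0625, so 6.25% more).

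**4. The age bands**

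| Place | Group | Rate per 100 PY |
|---|---|---|
| Sample Size Calculation | very high-risk MSM and TGW, 18–24 | 11 |
| Sample Size Calculation | high-risk MSM, 22–26 | 5 |
| Background | MSM and TGW who sold or exchanged sex, 18–21 | 11.1 |

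The first two rows overlap at ages 22 to 24. The first and third give nearly the same rate to different age bands.

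**The case against.** The strongest reply is that 8.5 may be the intended planning value. The range 7 to 10 is symmetric about 8.5, not about 8.0, so the loose element may be the 50/50 share. In that case stating a share of about 58/42 mends the text and changes no power figure. This stands, and it makes the loss of power conditional. It does not remove the inconsistency, because the text attributes 8.5 to the equal mixture. It is also true that 8.0 lies inside the stated range.

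Four stronger readings are tempting and are not supported:

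- **That the correction uses up all the slack.** With no inflation, Wald needs 577 PY per state at 8.5 and 613 at 8.0, which leaves 7 of 620. But Wald does not reproduce the plan's 620. Schoenfeld with no inflation needs 513 and then 545, which leaves 75.
- **That the low power at 20% inflation comes from this error.** Most of that fall is due to the inflation and is present at 8.5 already (Wald 82.8% to 67.8%). The mixture accounts for 2 to 3 points at each level.
- **That the rate of 11 was taken from ages 18 to 21 and wrongly extended to 24.** The strata are labelled by risk and population as well as age, so some overlap in age is possible. The two sections cite different references for their rates, and neither source is at hand. The overlap leaves the rate at 22 to 24 undefined but gives no direction of error.
- **That the true mixture is below 8.0.** That would replace the stated 50/50 share with an age distribution the article does not give.

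**Conclusion.** The section is internally inconsistent as written: an equal mixture of 11 and 5 is 8.0, and the sample size relies on 8.5. This needs no outside source.

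The consequence is modest and conditional. If 50/50, 11 and 5 are all right, expected infections are about 6% fewer (74 rather than 79 at 620 PY per state) and power is 2 to 3 points lower at each inflation level. On the reproducing calculation, power moves from 80.0% to 77.6%, which rests on the inferred 10% inflation. With no inflation it stays above 80% on both methods (80.5% and 84.8%). These levels assume that 620 means person-years.

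A reader might infer that the trial's power is simply overstated. The article does not support that without the condition, because it does not show whether the rate or the share is the slip. The age bands need to be reconciled, but they do not show that the rate of 11 is wrong.

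**What to change.** Do one of two things in Sample Size Calculation:

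- Replace 8.5 with 8.0 in both places, and restate the power at 620 PY per state or the person-years that 80% power requires (about 659 per state on the reproducing calculation).
- Keep 8.5, and state and justify the mixture of about 58/42 that produces it. No power figure then changes.

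In either case, state which incidence rate applies to ages 22 to 24, and reconcile the 18 to 24 band with the 18 to 21 band reported in Background. State the standard-error inflation actually used, so that the target can be checked.

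The cost is wording and one recalculation. Under the first option, the stated power falls by 2 to 3 points or the person-year target rises by about 6%.

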**Results:**

As of February 2019, 445 participants (417 MSM and 28 TGW) have contributed approximately 168 PY with 95% (73/77) retention at 12 months. 74.2% (330/445) of enrolled participants initiated PrEP at baseline, contributing to 134 PY of PrEP adherence, 1 PY nonadherence, and 33 PY PrEP nonuse/noninitiation. Some social harms, predominantly related to unintentional participant disclosure of PrEP use and peer stigmatization of PrEP and HIV, have been identified.

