### Combination Prevention Intervention

All participants will receive regular (every 3 months) HIV testing with risk-reduction counseling. Participants who have negative HIV rapid test results are counseled on the benefits of using PrEP in preventing HIV infection. This counseling includes a clear message on the efficacy of PrEP, discussion of barriers to initiating PrEP, and potential solutions to address these barriers. Although participants are not required to initiate PrEP as part of the study, study staff regularly promote the benefits of PrEP uptake. Condom and condom-compatible lubricant distribution occur at every study visit, including monthly medication pickups for those using PrEP. Syphilis, rectal gonorrhea, and chlamydia screenings with treatment for all identified infections are conducted every 6 months beginning at the baseline visit.

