## Discussion

This novel open-label study design and analytic plan will allow evaluation of the effectiveness and cost-effectiveness of combination prevention intervention for people who sell or exchange sex.

The vast majority of cisgender MSM and TGW who exchange sex and participate in this study thus far are interested in PrEP, report taking sufficient PrEP, and stay on PrEP, though additional efforts are needed to address community misinformation and stigma. Given the high interest and uptake of PrEP among young MSM and TGW who exchange sex, we anticipate that one limitation of the study will include the ability to enroll sufficient person-time of non-PrEP use. However, the high uptake, retention, and adherence that has not been observed in other PrEP demonstration projects may provide critical insights into method to improve the current PrEP continuum among MSM and TGW in other settings.

To our knowledge, this is one of the first studies to test the effectiveness of PrEP specifically for MSM and TGW who exchange sex. This study may answer important questions about the effectiveness of PrEP for those in high-risk contexts and the costs of providing such interventions. Furthermore, this study may identify optimal technology-based methods to support PrEP adherence among young populations with high transiency and occupations that would otherwise limit traditional in-person adherence support. In a setting where PrEP has received significant support by the government in HIV prevention and response, estimating the costs and cost-effectiveness of community-based implementation may have important implications for national approaches to bring PrEP to scale in Thailand.

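### Sample size assumes half of person-time on PrEP, but early data show 80%; at that split the 620 off-PrEP person-year goal is missed and 80% power depends on the optional extension

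*Protocol article*

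**What the plan says.** The Sample Size Calculation section rests on "incidence without PrEP is 8.5 per 100 PY, a PrEP efficacy of 50%, time-on-PrEP of 50%, attrition of approximately 2% per month", with "power=0.8, α (one-sided)=.025" and a standard error inflated by 0% to 20% for confounding adjustment. It arrives at 1,240, split 620 on and 620 off PrEP. The Abstract (Methods) gives the same 620/620 as the person-years that enrolment is meant to deliver; the Sample Size Calculation reads more like participants. The person-year reading is used here.

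The Abstract (Results) reports about 168 PY from 445 participants by February 2019, "contributing to 134 PY of PrEP adherence, 1 PY nonadherence, and 33 PY PrEP nonuse/noninitiation". Of these participants, 74.2% started PrEP at baseline. The Data Analysis section counts poorly adherent time as on PrEP in the primary comparison.

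Standard follow-up is 12 months. A further 12 months is offered as an option, if the timeline allows (Intervention Effectiveness Study Design; Recruitment and Consent). The Discussion says "we anticipate that one limitation of the study will include the ability to enroll sufficient person-time of non-PrEP use".

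**The concern.** The primary comparison needs enough infections in both kinds of person-time, and the off-PrEP rate is the reference. It also feeds the infections-averted figure in the cost-effectiveness analysis. The plan counts on half the time being off PrEP; the observed share is about a fifth.

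The design itself leans towards the observed split. Under Combination Prevention Intervention, "study staff regularly promote the benefits of PrEP uptake"; PrEP users are paid at each monthly pickup (Compensation); and non-users may start later.

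The article reports the imbalance and names it as a limitation, yet the 50% assumption, the 620/620 goal and the 80% power stand as written. A reader of an imprecise result could then set it against a power that the study did not have.

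**Working it through.** **Inputs.** From Sample Size Calculation: off-PrEP rate 0.085 per PY, ratio 0.50 (on-PrEP rate 0.0425), one-sided α 0.025, 1,240 participants, attrition 2% per month, SE inflation factor k = 1.0 to 1.2. From Results: 134 + 1 = 135 PY on and 33 PY off, of 168.

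**1. The plan's own figure.** Schoenfeld events at equal split: 4 × (1.960 + 0.842)² / (ln 0.5)² = 65.3, so 66. With 10% SE inflation, 66 × 1.21 = 79.9 events. The mean rate is (0.085 + 0.0425)/2 = 0.06375, so 79.9/0.06375 ≈ 1,253 PY, within 1% of 1,240. The plan's number therefore reproduces at about 10% inflation.

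The planned test is Wald, for which

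- SE = k × √(1/E_on + 1/E_off), where E is the expected number of infections;
- power = Φ(0.693/SE − 1.960).

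At 620/620 PY, E_on = 26.4 and E_off = 52.7, so SE = 0.239 at k = 1 and power is 83%. At k = 1.1 and 1.2 it is 75% and 68%.

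**2. Observed split.** On: 135/168 = 80.4%. Off: 33/168 = 19.6%.

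**3. Person-time from 1,240 participants.** PY per person over m months = (1 − 0.98^m) / (12 × 0.0202).

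- 12 months: 0.888 each, 1,101 PY in total, of which 19.6% is 216 off.
- 24 months for everyone: 1.585 each, 1,965 PY, 386 off.
- 24 months with no attrition: 2,480 PY, 487 off.

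Reaching 620 off-PrEP PY at this split would take 620/0.1964 ≈ 3,156 PY.

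**4. What would rescue the goal.** The remaining time would need an off-PrEP share of (620 − 33)/(1,240 − 168) = 55% at 1,240 total PY, or (620 − 33)/(1,965 − 168) = 33% at 1,965 PY.

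**5. Wald power for a ratio of 0.5** (k = 1.0 / 1.1 / 1.2):

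| Total PY | 50/50 split | 80/20 split | Infections on / off at 80/20 |
|---|---|---|---|
| 1,101 (12 months, attrition) | 78 / 70 / 63% | 68 / 60 / 53% | 37.6 / 18.4 |
| 1,240 | 83 / 75 / 68% | 73 / 65 / 58% | 42.3 / 20.7 |
| 1,965 (all 24 months, attrition) | 96 / 91 / 86% | 90 / 84 / 77% | 67.1 / 32.8 |

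For example, at 1,240 PY and 80/20, SE = √(1/42.3 + 1/20.7) = 0.268, and Φ(0.693/0.268 − 1.960) = Φ(0.62) = 73%.

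**6. Detectable ratio at 80% power, 80/20 split.** Solving the same power formula for the ratio, with E_on recomputed for each trial value: 0.44 / 0.40 / 0.36 at 1,101 PY, 0.47 / 0.43 / 0.39 at 1,240 PY, and 0.56 / 0.52 / 0.49 at 1,965 PY.

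**7. Total PY for 80% power at 80/20.** T = k² × (1.960 + 0.842)² / (ln 0.5)² × [1/(0.0425 × 0.804) + 1/(0.085 × 0.196)] = k² × 16.34 × 89.2. This gives 1,457, 1,763 and 2,098 PY for k = 1.0, 1.1 and 1.2, of which 286, 346 and 412 PY are off PrEP.

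**The case against.** A reader might infer that 620 off-PrEP PY is out of reach and that the stated power is therefore lost. The documents support neither as a flat statement.

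- **The split may move.** It comes from 168 PY, about 14% of 1,240 and 0.38 PY per participant, when the effectiveness study had launched only in Bangkok. Participants may stop PrEP at any time. The shares in step 4 may be unlikely, but they are not impossible.
- **Missing 620 is not losing 80% power.** Off-PrEP time is richer in infections, so far fewer than 620 off-PrEP PY can suffice if total follow-up is long enough. At 1,965 PY the 80/20 split still gives 90/84/77%.
- **Retention is better than planned.** It was 95% (73/77) at 12 months, against 78% implied by 2% a month. If 95% a year held and half of those retained extended, total time would be about 1,783 PY and power 87/80/73%.
- **Not all of the shortfall comes from the split.** At 20% inflation, power is already 68% with 620/620 PY. The split costs about 10 percentage points at 1,240 PY.
- **The authors disclosed the risk**, and nothing in the Data Analysis section uses planned power to interpret results. Lost precision will show in the standard error.

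All of this stands, and it limits the point. It does not remove it. Even at 95% retention, 12 months gives only about 1,209 PY and roughly 72% power with no inflation. The Sample Size Calculation does not say that its power depends on the extension, and naming a limitation does not update the figures that it affects.

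**Conclusion.** The point holds in conditional form. The 50% assumption and the 620/620 goal do not match the article's own person-time, and neither they nor the power were revised. If the 80/20 split persists, off-PrEP time will be about 216 to 487 PY depending on follow-up and attrition, not 620. Power for a ratio of 0.5 is 53% to 68% under standard 12-month follow-up with planned attrition, and 77% to 90% if every participant completes the extension period under that attrition. Whether 80% is achieved therefore turns on uptake of the optional second year and on how much confounding adjustment inflates the standard error.

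This rests on the plan's rate of 8.5 per 100 PY, its 50% effect, a Wald test on the log rate ratio, and an early split that may change. Over the plan's own range of 7 to 10 per 100 PY, power at 1,240 PY and 80/20 is 65% to 80% with no inflation and 50% to 65% with 20%. The point concerns the stated target and power. It does not affect the endpoint, the estimator or data collection.

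**What to change.** Before incidence by PrEP status is reviewed:

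1. Restate power and detectable hazard ratio at the observed split for the three totals above (1,101, 1,240 and 1,965 PY) at 0, 10 and 20% inflation, and say which rely on the extension.
2. Replace the 620/620 goal with a total person-year target at the realised split: about 1,457 PY with no inflation, 1,763 at 10% and 2,098 at 20%. State which inflation is assumed and update the target if the split moves.
3. Pursue it through the 12-month extension already offered, without added enrolment. The 2,098 PY figure exceeds the 1,965 PY available at planned attrition, so it also needs retention better than planned.
4. If the target is not met, report the lower power and base conclusions on the confidence interval for the hazard ratio.

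The cost is an amendment to the sample-size text, a less favourable stated power, and open reliance on extended follow-up. The offer of PrEP is untouched.

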**Methods:**

This open-label, nonrandomized assessment compares the relative effectiveness of a combination prevention intervention with and without daily oral emtricitabine and tenofovir disoproxil fumarate (Truvada) PrEP with SMS-based adherence support. HIV-uninfected young MSM and TGW aged 18 to 26 years in Bangkok and Pattaya who self-report selling/exchanging sex at least once in the previous 12 months are recruited by convenience sampling and peer referral and are eligible regardless of their intent to initiate PrEP. At baseline, participants complete a standard assessment for PrEP eligibility and may initiate PrEP then or at any time during study participation. All participants complete a survey and HIV testing at baseline and every 3 months. Participants who initiate PrEP complete monthly pill pickups and may opt-in to SMS reminders. All participants are sent brief weekly SMS surveys to assess behavior with additional adherence questions for those who initiated PrEP. Adherence is defined as use of 4 or more pills within the last 7 days. The analytic plan uses a person-time approach to assess HIV incidence, comparing participant time on oral PrEP to participant time off oral PrEP for 12 to 24 months of follow-up, using a propensity score to control for confounders. Enrollment is based on the goal of observing 620 person-years (PY) on PrEP and 620 PY off PrEP.

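### The 80% power is stated against standard-error inflation of 0% to 20%, but 620 + 620 person-years deliver it only up to about 4% to 10%, and the 1240 is given in two different units

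*Protocol article*

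**What the plan says.** The Sample Size Calculation section sets out these assumptions: "incidence without PrEP is 8.5 per 100 PY", a halving of incidence on PrEP, half of the time spent on PrEP, attrition of about 2% per month, power of 0.8, "α (one-sided)=.025", and "inflation of the standard error of the hazard ratio by 0% to 20% after adjusting for confounding". It calls the result 1240 participants and concludes: "we expect that a combined sample of 1240 (620 on PrEP and 620 not on PrEP) will be sufficient".

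The Methods paragraph of the abstract gives the same numbers as person-time: "Enrollment is based on the goal of observing 620 person-years (PY) on PrEP and 620 PY off PrEP".

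The Intervention Effectiveness Study Design section sets standard follow-up at 12 months, with an optional further 12. The Recruitment and Consent section makes the second year depend on the study timeline. The Data Analysis section specifies a Wald test of the PrEP coefficient.

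**The concern.** One power figure is attached to a whole range of standard-error inflation. Power falls as the standard error grows, so a single sample cannot give 80% at both ends of the range. Either 80% is the value at the unfavourable end and the study does better elsewhere, or it applies at some unstated point and the study does worse above it.

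This matters because the comparison is between self-selected states. The Data Analysis section plans inverse probability weights for treatment and for censoring, so no inflation at all is the least plausible case. If the adjusted analysis shows no difference, readers will judge it against 80% power.

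The change of unit compounds this. With attrition, 1240 participants followed for one year do not supply 1240 person-years.

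**Working it through.** **Inputs.** From the Sample Size Calculation section: incidence off PrEP 0.085 per PY; hazard ratio 0.5, hence 0.0425 per PY on PrEP; equal person-time; one-sided alpha 0.025 (z = 1.960); power 0.80 (z = 0.842); attrition 2% per month; inflation factor f from 1.0 to 1.2 on the standard error. From the abstract: 620 PY in each state.

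**Reproducing the plan's figure.** Schoenfeld's formula with an equal split:

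- Events needed without inflation: 4 × (1.960 + 0.842)² / (ln 0.5)² = 65.3.
- Events per PY in each state, both states added: 0.085 + 0.0425 = 0.1275.
- PY per state: 65.3 / 0.1275 = 512.5 at f = 1.0; × 1.21 = 620.1 at f = 1.1; × 1.44 = 738.0 at f = 1.2.

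The stated 620 + 620 therefore comes out at 10% inflation, the midpoint of the range, counted in person-years.

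**Expected events at the stated goal.** Off PrEP 620 × 0.085 = 52.7; on PrEP 620 × 0.0425 = 26.35; total 79.05.

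**Power at 620 + 620 PY.**

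- Wald: SE = √(1/26.35 + 1/52.7) = 0.2386; power = Φ(0.6931 / (0.2386 f) − 1.960).
- Schoenfeld: power = Φ(√(79.05 × 0.25) × 0.6931 / f − 1.960).

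| SE inflation | Wald | Schoenfeld |
|---|---|---|
| 0% | 82.8% | 86.9% |
| 10% | 75.2% | 80.0% |
| 20% | 67.8% | 72.8% |

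A Poisson simulation of the Wald test gave 84.7% with no inflation and 69.5% at 20% (events scaled down by 1.44), between the two columns.

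**Inflation at which power reaches 80%.** Wald: 0.6931 / 0.2386 / 2.802 = 1.037, so about 4%. Schoenfeld: √(79.05 / 65.3) = 1.10, so about 10%.

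**Person-time needed for 80% at 20% inflation.** Schoenfeld 738 PY per state (1476 in all). Wald: 1.44 × 2.802² × (1/0.085 + 1/0.0425) / 0.6931² = 830 PY per state (about 1661 in all).

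**Sensitivity to incidence.** Over the article's own range of 7 to 10 per 100 PY, power at 20% inflation is 59% to 64% at 7 and 74.7% to 79.5% at 10 (Wald to Schoenfeld).

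**Reading 1240 as participants.** With a constant 2% monthly loss, mean follow-up over 12 months is (1 − 0.98¹²) / (−12 ln 0.98) = 0.888 years, and over 24 months 1.585 years.

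- 12 months only: 1240 × 0.888 = 1101 PY. Power at 0/10/20% inflation is 78/70/63% (Wald) or 83/75/68% (Schoenfeld).
- All retained participants take the second year: 1240 × 1.585 = 1965 PY. Power at 20% inflation is 86% (Wald) or 90% (Schoenfeld).
- The second year adds at most 1965 − 1101 = 864 PY. Share of retained participants who must extend: (1240 − 1101) / 864 = 16% to reach 1240 PY; (1476 − 1101) / 864 = 43% (Schoenfeld) to (1661 − 1101) / 864 = 65% (Wald) to reach 80% power at 20% inflation.

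**The case against.** The best defence is that 1240 was not miscalculated. A standard formula with the article's inputs returns 620 PY per state at the centre of the inflation range, and sizing at the centre of an uncertain range is a legitimate choice. The text does not expressly promise 80% at the 20% end. That stands: a reader might infer that 1240 has no basis, and the figures do not support this. What remains is that the article never says 80% belongs to about 10% inflation, and it gives no lower power for the upper half.

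A second defence is the optional second year. A reader might infer that the study must be underpowered at 20% inflation, or that attrition is simply not allowed for. Neither follows. If the goal is observed person-years, attrition is absorbed by definition. If it is 1240 participants, modest extension (about 16%) restores 1240 PY, and extension by about 43% to 65% would give 80% power even at 20% inflation. But extension is optional, depends on the timeline, and no uptake is stated.

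A third defence is that a journal article condenses. This would excuse a missing derivation. It does not excuse one power set against a range over which it does not hold, or one number in two units.

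It can also be said that imbalance in person-time is the larger threat: the Results show about 135 of 168 PY on PrEP, and the Discussion anticipates too little time off PrEP. That is so, but it does not make the stated power right.

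**Conclusion.** The power statement is wrong as written and should be fixed, though it is not a fatal fault. At 620 + 620 PY, 8.5 per 100 PY and a hazard ratio of 0.5, power is at least 80% only up to about 4% (Wald) or 10% (Schoenfeld) inflation, and is about 68% to 73% at 20%. Neither formula gives 80% at 20% inflation anywhere in the stated incidence range.

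This rests on an equal split of person-time and on reading the 20% as the article words it, on the standard error. If variance had been meant, power would be 75.6% (Wald) to 80.3% (Schoenfeld). That the sample was sized at the 10% midpoint is an inference from the match with 620, not something the article states. The participant-based figures also assume a constant 2% monthly loss continuing through the second year.

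**What to change.** Three changes of wording:

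1. State the size in person-years throughout, so that the abstract and the Sample Size Calculation section agree.
2. Replace the single power with power by inflation level, naming the formula: at 0%, 10% and 20% inflation, 620 + 620 PY give 83%, 75% and 68% (Wald) or 87%, 80% and 73% (Schoenfeld). Alternatively, if Schoenfeld at the midpoint was indeed the basis, say that 80% applies at about 10% inflation and falls to about 68% to 73% at 20%. The Wald values should not be printed alone, since Schoenfeld is the formula that reproduces the plan's number.
3. State the uptake of the second year that the person-year goal assumes, with the 12-month yield of about 1101 PY from 1240 participants beside it.

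No extra enrolment, test or analysis follows from this. The cost is a less favourable power statement at the upper end of the inflation range.
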